**Methods:**

This is an open-label Phase 4 clinical trial of LDX in adults with moderate to severe BED. Enrolment will include 40 adults with moderate to severe BED aged 18–40 years and Body Mass Index (BMI) of 20–45 kg/m^2^, and 22 healthy controls matched for age, gender and BMI. Clinical interview and validated scales are used to confirm diagnosis and screen for exclusion criteria, which include comorbid anorexia nervosa or bulimia nervosa, use of psychostimulants within the past 6 months, and current use of antipsychotics or noradrenaline reuptake inhibitors. Baseline assessments include clinical symptoms, multimodal neuroimaging, cognitive assessment of reward sensitivity and behavioural inhibition, and an (optional) genetic sample. A subset of these assessments are repeated after eight weeks of treatment with LDX titrated to either 50 or 70 mg. The primary outcome measures are resting-state intrinsic connectivity and the number of binge eating episodes. Analyses will be applied to resting-state fMRI data to characterise pharmacological effects across the functional connectome, and assess correlations with symptom measure changes. Comparison of neural measures between controls and those with BED post-treatment will also be performed to determine whether LDX normalises brain function.

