It is widely recognised that cognition and behaviour arise from the dynamic interactions of distributed brain areas operating in networks. These large-scale networks can be imaged during functional tasks that evoke their activity, or during rest, when they tend to produce highly synchronised, very low frequency neuronal oscillations [25]. Analysis of resting-state functional magnetic imaging (rs-fMRI) can reveal much about the innate organisation of the brain, by demonstrating how brain regions, or nodes, are organised within networks, and how various networks are intrinsically connected with one another [26]. Applying a connectomic approach increases potential for providing new insights into the neural mechanisms of pharmacotherapy by providing comprehensive descriptions of these intrinsic connectivity patterns [27, 28].

There are currently no studies published on intrinsic connectivity patterns in BED relative to controls. As such, it is difficult to hypothesise precisely how LDX will effect neural connectivity in this group. Given the known dysfunction in the fronto-striatal regions relating to reward and inhibition in BED, it is assumed however that effective treatment with LDX will “normalise” activity and connectivity within these networks. We will also be able to examine relationships between treatment-driven neural changes and a large range of symptom measures and objective laboratory-based measures of cognition. These secondary meaures may also help to determine whether LDX exerts beneficial effects more broadly to non-food inhibitory control and other general cognitive improvements.

The primary aim of this study is to provide a comprehensive understanding of the neural mechanisms by which LDX improves symptoms of BED. We hypothesise that LDX will act by normalising connectivity within and between brain circuits responsible for reward and impulse control. Further, we hypothesise that a reduction in binge eating behaviours will correlate with normalised activity and connectivity of brain regions within reward and impulse control networks. Secondary aims include examining treatment-related changes in cognitive performance and other self-reported measures of symptoms and behaviour.

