## Method

### Participants

Approximately 40 participants with BED and 22 healthy matched controls will be recruited into the study. Both BED and control participants must be between 18 to 40 years of age (inclusive), and have a BMI between 20 to 45 kg/m^2^ (inclusive). BED participants are required to have a diagnosis of moderate to severe BED. This is based on Module I of the *Structural Clinical Interview for DSM-5 Research Version* (SCID-5-RV) [29]. Consistent with LDX efficacy studies [18, 19], moderate to severe BED severity requires a minimum of three days of binge eating per week in the past month and a minimum score of 4 on the *Clinical Global Impression – Severity* scale (CGI-S) [30], a clinician-determined summary measure of a patient’s global functioning. The *MINI International Neuropsychiatric Interview Version 7.0.2 for DSM-5* [31] (MINI) is also used to assess comorbid psychiatric disorders to determine eligibility and better characterise the cohort. The full inclusion and exclusion criteria for BED and control participants are listed in Tables 1 and 2.

**Table 1 Tab1:** Inclusion and exclusion criteria for BED participants

Criteria	List
Inclusion	• Age 18–40 years.
	• BED diagnosis, confirmed by the eating disorders module of the Structured Clinical Interview for DSM-5.
	• Moderate to severe BED, defined as the presence of binge eating frequency of ≥3 days/week in the month prior to the baseline assessment and a score of ≥4 on the clinical global impressions severity scale.
	• BMI of 20 – 45 kg/m^2^.
	• A study doctor has verified that it is medically and psychiatrically safe for their patient to commence LDX.
	• Fluent in English.
	• Have provided written informed consent.
Exclusion	• History of psychosis or mania.
	• Pregnant or breast-feeding women.
	• Current therapy with antipsychotics or noradrenaline reuptake inhibitors.
	• Current therapeutic intervention specific to treating eating behaviours and/or cognitions.
	• Cardiovascular disease, hypertension, use of monoamine oxidase inhibitors, or any other contraindications for psychostimulants.
	• History of substance abuse/dependence (excluding nicotine).
	• Previous suicide attempts or current suicidal ideation.
	• Known medical condition, disease or neurological disorder which might, in the opinion of investigator/s, interfere with the assessments to be made in the study or put BED patients at increased risk when exposed to optimal doses of the drug treatment.

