### Overall study design

This study is a repeated-measures pre-post treatment design. Repeated-measures data from a control group is being collected at week 0 and week 8 for normative comparisons. Figure 1 outlines the timeline of events.

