### Data analysis

Only the data from individuals with a medication compliance rate of ≥60% will be included in primary outcome analyses. For all analyses, a *p* value of < 0.05 will be considered statistically significant and relevant corrections for multiple comparisons will be applied.

Framewise displacement—movement of the head from one volume/timepoint to the next—and scaled signal intensity differences between contiguous volumes, will be calculated for each rs-fMRI time series during the quality control process. Temporal masks will be applied to censor volumes including motion, and participant data will be excluded from analyses if more than 1/3 of the time course data requires temporal masking.

Functional connectomics involves the study of brain connectivity, first by identifying the nodes (distinct brain regions) and subsequently estimating the functional connections (network edges) between these nodes [51]. Both voxel-wise and brain atlas parcellation approaches (e.g. Gordon parcellations) [52] will be utilised to designate nodes. Data-driven, whole-brain analyses using methods such as multivariate distance matrix regression [53] and network based statistics [54] will then be applied to rs-fMRI data to characterise pharmacological effects across the functional connectome, and assess correlations with symptom measure changes. Using a similar approach to Yang et al. [55], the results of data-driven analyses will be followed up using seed-based functional connectivity analyses. Connectomic measures will be computed for BED participants at baseline and post-treatment. A paired-sample t-test will be performed to compare baseline and post-treatment connectivity profiles to confirm the treatment effect. To examine any normalisation effects of LDX in BED participants, two independent sample t-tests will be conducted to compare functional connectivity between healthy controls, and the BED group at baseline and post-treatment, respectively. To examine the association of changes in functional connectivity and clinical improvement, we will correlate change scores (Δ = BED post-treatment – BED baseline) of functional connectivity with changes in the number of binge-eating episodes.

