## Discussion

The combination of neuroimaging and laboratory-based cognitive measures will provide a sophisticated and comprehensive explanation of the neural mechanisms by which LDX improves BED symptomology. The repeated measures design will enable participants to act as their own controls in assessing whether LDX changes interconnectivity and integration, particularly in brain regions responsible for reward sensitivity and impulse control. We can also assess whether interconnectivity and integration post-treatment more closely resembles healthy controls, relative to pre-treatment.

A limitation of this study is that we are unable to draw absolute conclusions on the causality of LDX in our results as the design does not include a placebo arm. There are confounding factors that could contribute to changes in neural connectivity and binge eating symptomology, for instance, use of a self-monitoring diary, clinician-patient interaction during study assessments and other social and environmental factors. While we may not be able to attribute changes in BED symptomology and neural connectivity solely to the effects of LDX, the results are more generalisable to a real-world setting where these factors exist and contribute to treatment effects. As this study is not designed to assess treatment efficacy, accounting for placebo effect is not required. Another limitation is that the primary measure of binge-eating behaviour, the number of binge eating events, is based on self-report, which relies on memory and unbiased reporting for accuracy. Finally, more information is required on the longer term efficacy and safety implications of LDX treatment, however this is beyond the scope of the current study and should be a direction for future research.

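### Normalisation of connectivity is examined by two separate BED-versus-control t-tests, neither of which tests whether the gap to controls narrowed

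*Protocol article*

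**What the plan says.** The Background section states the hypothesis under the primary aim: "We hypothesise that LDX will act by normalising connectivity within and between brain circuits responsible for reward and impulse control". Resting-state connectivity is one of the two primary outcomes.

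The Data analysis section gives three relevant tests. The first is within BED: "A paired-sample t-test will be performed to compare baseline and post-treatment connectivity profiles to confirm the treatment effect". The other two are assigned to normalisation: "two independent sample t-tests will be conducted to compare functional connectivity between healthy controls, and the BED group at baseline and post-treatment, respectively". The Abstract gives the second of these a decisive role: "Comparison of neural measures between controls and those with BED post-treatment will also be performed to determine whether LDX normalises brain function". The Discussion puts the question in relative terms: "whether interconnectivity and integration post-treatment more closely resembles healthy controls, relative to pre-treatment".

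On the data available, the Participants section says "Approximately 40 participants with BED and 22 healthy matched controls will be recruited into the study", and the Overall study design section says "Repeated-measures data from a control group is being collected at week 0 and week 8 for normative comparisons". The Post-treatment session section lists the assessments not repeated at week 8; resting-state fMRI is not among them. Data analysis also plans a two-group comparison of change scores, but describes it with the secondary measures, for the tasks, to deal with practice effects.

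**The concern.** Whether BED moved closer to controls is a question about a change in a difference. Two separate tests, one at each visit, do not answer it. A significant result followed by a non-significant one is not a test of change, and a non-significant result in a small comparison does not show similarity.

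The sample-size section justifies only the within-subject comparison, so its stated power does not carry over to the comparison with 22 controls. The within-BED paired test speaks to change, but it is given a different purpose (confirming the treatment effect) and it ignores the controls. At stake is the study's main mechanistic claim: as the section stands, that claim rests on no single test with a known error rate.

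**Working it through.** **Inputs.** From the document: about 35 evaluable BED participants, 22 controls, two-sided alpha 0.05, effect size 0.5. Assumed, because the document does not give them: the BED-control gap (0.5 or 0.8 SD), the week-0 to week-8 correlation r (0.3 to 0.7), no loss of controls, and one connectivity measure without multiplicity correction.

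**1. The plan's own figure.** Paired t-test, n = 35: noncentrality 0.5 × √35 = 2.96 on 34 df gives power 82.0%. The stated figure of approximately 80% is reproduced.

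**2. The comparison with controls.** Standard error in SD units: √(1/35 + 1/22) = 0.272. Noncentrality 0.5/0.272 = 1.84 on 55 df gives power 43.9%, so an unchanged 0.5 SD gap is non-significant at week 8 in 56% of trials (81% at 0.3 SD, 18% at 0.8 SD). Power of 80% needs a gap of about 0.78 SD. The 95% interval half-width is 2.004 × 0.272 = 0.55 SD.

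**3. Neither group changes.** Simulation, 40,000 trials per setting. The table gives the share of measures significant at baseline that show each pattern. The first figure uses the baseline control scan at both visits; the second uses the week-8 control scan for the second test.

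| Gap | r | Week 8 non-significant | Also a significant paired change towards controls |
|---|---|---|---|
| 0.5 | 0.3 | 27.3% / 44.7% | 3.3% / 3.6% |
| 0.5 | 0.5 | 23.4% / 37.6% | 3.0% / 3.0% |
| 0.5 | 0.7 | 18.0% / 28.3% | 2.4% / 2.4% |
| 0.8 | 0.3 | 9.6% / 15.0% | 1.4% / 1.3% |
| 0.8 | 0.5 | 7.8% / 12.5% | 1.1% / 1.1% |
| 0.8 | 0.7 | 6.2% / 10.0% | 0.8% / 0.8% |

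The group-by-session contrast on change scores rejected in 4.8 to 5.1% of trials.

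**4. Both groups shift alike.** Now let both groups move by the same amount, in the direction that lowers the BED value, with the 0.5 SD gap unchanged. For an assumed shift of 0.25 SD, and requiring the paired result as well, 22 to 44% of measures significant at baseline show the full normalisation pattern. The lower end applies when the week-8 control scan is the comparator and the upper end when the baseline scan is reused. For shifts of 0.2 to 0.3 SD (r 0.5 to 0.7) the ranges are 17 to 26% and 24 to 58%. The group-by-session contrast stays at 5%.

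**5. Cost of the direct test.** Suppose a 0.5 SD gap closes fully. The SD of change is √(2(1 − r)), which is 1 at r = 0.5. The paired test then has noncentrality 2.96 (power 82%), and the group-by-session contrast 0.5/0.272 = 1.84 (power 44%). Requiring a significant baseline difference as well, the contrast succeeds in 27 to 34% of trials for r 0.5 to 0.7, against 37 to 41% for the three planned tests read together.

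**The case against.** The strongest reply is that the plan already contains a test of change. If the same control scan is the reference at both visits, the change in the gap is (BED week 8 − control) − (BED week 0 − control), which is simply the paired change in BED. Read that way, the false pattern when neither group changes is about 2.4 to 3.6% of measures significant at a 0.5 SD baseline gap. The proposed rule gives about 4 to 5% in the same setting, so it is no stricter there. This stands.

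It does not dispose of the point. The section does not make normalisation depend on the paired result. The paired test also cannot remove a shift shared with controls, a kind of effect the plan itself allows for in the tasks.

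A reader might infer more than the text supports:

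- **That the plan would declare normalisation when nothing changed, because a non-significant week-8 test will be read as normalisation.** No such rule is written. The Abstract's wording leans that way but states no criterion, and the 18 to 45% rates at a 0.5 SD gap describe a plan without the paired test.
- **That 40 and 22 participants cannot be matched, or that the comparison will be unadjusted.** Unequal numbers rule out one-to-one pairing, not group matching, which is ordinary. Nothing says that covariates will be omitted.

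**Conclusion.** The point holds in a limited form. The two t-tests named for normalisation do not test whether the BED-control gap narrowed, and a non-significant week-8 result is weak evidence of similarity. The paired test largely covers the case in which neither group changes, provided it is read jointly. What remains is that the plan does not require that joint reading, and that a session effect common to both groups could pass for normalisation in 22 to 44% of measures significant at baseline, if the shared shift were 0.25 SD and the gap 0.5 SD.

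The size rests on assumed gaps, correlations and shifts. The document gives none of these, and a shared shift is a possibility rather than something it reports. Correction for multiple comparisons or loss of controls would lower the power of the control comparison further.

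**What to change.** In Data analysis, extend the two-group change-score (group by session) analysis planned for tasks to the resting-state connectivity measures, using the control scans at weeks 0 and 8. Base a claim of normalisation on two results: a BED-control difference at week 0, and a group-by-session change that moves that difference towards controls. Report the week-8 BED-minus-control difference with its 95% confidence interval, and state that non-significance at week 8 alone is not evidence of normalisation. The paired t-test can stay as the test of change within BED. Covariate adjustment is optional.

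No new data are needed, because controls are already being assessed at both visits. The cost is power: with 22 controls the group-by-session contrast is weaker than the paired test (44% against 82% at r = 0.5 for full closure of a 0.5 SD gap), so the claim becomes harder to make.

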	• Use of a psychostimulant in the 6 months prior to the study.
	• Inability to tolerate the MRI scanner due to physical or psychological factors.
	• History of physical brain injury or blow to the head that resulted in loss of consciousness for at least 10 min.

**Table 2 Tab2:** Inclusion and exclusion criteria for control participants

Criteria	List
Inclusion	• Age 18–40 years.
	• BMI of 20 – 45 kg/m^2^.
	• Fluent in English.
	• Have provided written informed consent.
	• Current or previous diagnosis of an eating disorder or any other psychiatric diagnosis, including substance dependence.
Exclusion	
	• Pregnant or breast-feeding women.
	• Inability to tolerate the MRI scanner due to physical or psychological factors.
	• Known medical condition, disease or neurological disorder which might, in the opinion of investigator/s, interfere with the assessments to be made in the study or put subjects at increased risk.
	• History of physical brain injury or blow to the head that resulted in loss of consciousness for at least 10 min.
	• Prior treatment with any stimulant medication.

Participants are being recruited via referral by participating clinicians or self-referral due to online advertisements through Facebook, volunteer job sites, and webpages of universities in the Sydney metropolitan area.

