### Intervention

BED participants complete an 8 week course of LDX. The dose schedule for LDX is based on existing clinical practice and efficacy literature [18, 19]. All participants commence with 30 mg/day of LDX, and are advised to take it at the same time each morning. Participants are provided with self-monitoring sheets to help track their medication compliance.

After 2 weeks, participants will increase their dose to 50 mg/day if there are no abnormal changes to their blood pressure and heart rate. After 4 weeks, participants may continue with 50 mg/day or increase to 70 mg/day depending on their responsiveness to medication and symptom severity. Participants will remain on this dosage for another 4 weeks. At the week 8 follow-up session, participants will be required to return the completed self-monitoring sheets and any unused tablets. Participants with a compliance rate of less than 60% following a count of unused tablets will be viewed as non-compliant, and their data will be excluded from analysis.

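### Normalisation is examined with two separate BED-versus-control t-tests, neither of which tests whether BED connectivity moved closer to controls, and a general stimulant effect could be read as normalisation

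*Protocol article*

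**What the plan says.** The main hypothesis, in Background, is about normalisation: "We hypothesise that LDX will act by normalising connectivity within and between brain circuits responsible for reward and impulse control". The Abstract states what the control comparison is for: "Comparison of neural measures between controls and those with BED post-treatment will also be performed to determine whether LDX normalises brain function". The Discussion states the same aim as a change over time: "We can also assess whether interconnectivity and integration post-treatment more closely resembles healthy controls, relative to pre-treatment".

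Data analysis names the procedure: "two independent sample t-tests will be conducted to compare functional connectivity between healthy controls, and the BED group at baseline and post-treatment, respectively". It also plans a paired t-test of baseline against post-treatment connectivity within BED, and a correlation of connectivity change with change in binge-eating episodes. No rule says how the two control comparisons combine into a conclusion.

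On treatment, Intervention says "BED participants complete an 8 week course of LDX". The control exclusion criteria (Table 2) include "Prior treatment with any stimulant medication". Controls are scanned twice: "Repeated-measures data from a control group is being collected at week 0 and week 8 for normative comparisons". The Discussion concedes that "the design does not include a placebo arm" and that changes may not be due solely to LDX, giving the diary, clinician contact and social or environmental factors as examples.

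**The concern.** The stated question is whether the gap between BED and controls shrinks. The stated tests ask whether there is a gap at week 0 and whether there is a gap at week 8. A significant first result followed by a non-significant second one is easily read as normalisation, but it can arise with no change at all.

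The design adds a second problem. At week 8, medicated BED participants are compared with controls who have never taken a stimulant. If LDX shifts connectivity in anyone, some of that shift will oppose baseline BED differences and some will not. The first part looks like correction of a BED abnormality. The limitation paragraph covers changes that LDX did not cause. It does not cover a change that LDX did cause but that has nothing to do with BED. The sample size section itself cites strong connectivity effects of a related stimulant, so a sizeable drug effect is expected.

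At stake is the study's central conclusion, that LDX normalises brain function.

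**Working it through.** **1. Question against tests.** Let G0 and G8 be the BED-minus-control difference at week 0 and week 8. The two planned t-tests have null hypotheses G0 = 0 and G8 = 0. The paired test has the null that the BED mean did not change. The question is whether |G8| < |G0|, and no stated test addresses it. The group comparison of change scores later in Data analysis is set for the tasks, to allow for practice effects. As controls are untreated, it could not separate drug from disorder in any case.

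**2. Power.** The plan's figure is about 80% for n = 35, d = 0.5, two-sided 0.05. For a paired t-test the noncentrality is 0.5 × √35 = 2.96 on 34 df, giving 82%. The figure is reproduced, but it applies to the within-BED comparison. For 35 BED v 22 controls the noncentrality at d = 0.5 is 0.5 / √(1/35 + 1/22) = 0.5 / 0.272 = 1.84 on 55 df, giving 44%. Power of 80% needs d = 0.78. Non-significance at week 8 is therefore weak evidence that a gap has closed.

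**3. Simulation, no drug effect.** From the plan: 35 BED, 22 controls, two-sided 0.05. Assumed: 20,000 independent unit-variance connections, retest correlation 0.5, true gaps normal with SD 0.2 or 0.3, no multiplicity correction. With LDX doing nothing, about 63% (gap SD 0.2) and 49% (gap SD 0.3) of baseline-significant connections are non-significant at week 8. Repeat runs ranged from 47 to 64%. With gaps of 0.6 to 0.8 SD in a tenth of 300 connections, and one control sample used for both sessions, the loss was 35 to 25%.

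**4. Simulation, non-specific drug effect.** Add an LDX effect of SD 0.3 or 0.5, unrelated to the gap. The share losing significance is 46 to 57%, no higher than with no drug, so that share says nothing about LDX. A stricter pattern does respond to the drug: lost significance plus a significant paired change towards controls. It occurs for about 4 to 5% of baseline-significant connections with no effect and 19 to 27% with a non-specific one.

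**5. Distance over the same runs.** The mean absolute value of a normal variable with SD s is 0.798 s. The gap SD is g at week 0 and √(g² + L²) at week 8, where L is the SD of the LDX effect.

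| g | L | week 0 | week 8 |
|---|---|---|---|
| 0.2 | 0.3 | 0.160 | 0.288 |
| 0.3 | 0.3 | 0.239 | 0.339 |
| 0.2 | 0.5 | 0.160 | 0.430 |
| 0.3 | 0.5 | 0.239 | 0.465 |

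The simulated rises were 42 to 167%. Newly different connections outnumbered those that lost significance by 2.2 to 5.3 to 1.

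**6. The direction is not fixed.** Let a fraction f of connections start 0.8 SD below controls and let LDX add 0.5 SD everywhere. The mean squared gap is 0.64f at week 0 and 0.09f + 0.25(1 − f) at week 8.
- f = 0.1: root mean square 0.253 to 0.484, a rise.
- f = 0.5: 0.566 to 0.412, a fall.
- f = 0.8: 0.716 to 0.349, a fall.

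The two are equal at f = 0.25 / 0.80 = 0.31. In the simulated f = 0.1 case, about 26 of 38 baseline-significant connections (68%) lost significance, some 24 of them with a significant paired change towards controls, although distance rose in every run. With the shift in the same direction as the deviation, only 17% lost significance.

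**The case against.** Several points on the other side stand.

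- **Unit of analysis.** A reader might infer that normalisation is judged only connection by connection. The text does not say so. Data analysis names multivariate distance matrix regression, network-based statistics and seed-based follow-up, and the measures section adds global graph metrics. This does not close the gap, because no test of change in distance to controls is stated for any of them.
- **Reporting.** A reader might infer that a non-specific effect would be reported as normalisation. The plan fixes no such rule, and the post-treatment comparison would itself show newly different connections. It could be read that way; no more can be said.
- **Overall direction.** A reader might infer that BED moves further from controls overall. In step 5 that follows from the assumption, since adding an independent effect always widens the mean gap. Step 6 shows that it can go the other way.
- **Correction.** The plan promises correction for multiple comparisons, which the main simulation omits. With false discovery rate control, gap SD 0.2 left only 0 to 23 of 20,000 connections significant at baseline. Gap SD 0.3 left 467 to 605, and 77 to 131 showed the stricter pattern when LDX acted. Correction shrinks the problem but does not remove it.
- **Remedy.** A distance test still compares medicated with untreated people. A general shift that opposes the BED pattern would lower the distance.

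The last objection is that a distance metric belongs in a fuller analysis plan. That is fair for the choice of metric. But the article itself names both the tests and the conclusion to be drawn from them, and the two do not match.

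**Conclusion.** The point holds in this form. The stated tests do not address whether BED connectivity moved closer to controls, and the design cannot tell correction of a BED abnormality from a general stimulant effect. Loss of significance should not count as normalisation, since about half or more of baseline-significant connections lose it with no drug effect under the main assumptions. Requiring a significant paired change as well does not protect the conclusion: the pattern rises from about 4 to 5% to 19 to 27% under an effect unrelated to BED.

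The sizes rest on assumed effect SDs, retest correlation 0.5, independent connections and uncorrected testing, none of which the protocol supplies. Whether net distance rises or falls cannot be told from the documents. No stated figure is wrong.

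**What to change.** Name one deciding test of normalisation. For each BED participant, compute the distance between their connectivity pattern and the mean control pattern of the same session, at week 0 and week 8. Do this within the reward and impulse-control circuits of the hypothesis, with their regions listed in advance, and for the whole profile. Test the mean change in distance, with the change in controls' leave-one-out distances as reference. Report connections moving away from controls beside those moving towards them. Use the word *normalises* only where the tested distance falls; otherwise report that connectivity changed.

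Add to the limitations that, without treated non-BED participants, a general stimulant effect cannot be excluded even when distance falls.

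The cost is a change of wording and a short extra computation on scans already planned at both weeks for both groups. The downside is a possibly weaker claim.
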